## 2. Materials and Methods

### 2.1. Study Design

This is a cross-sectional, vignette-based experiment with a four-level within-subjects (repeated-measures) design. Vignette experiments combine the internal validity of experimental manipulation with survey feasibility and are an established method for isolating drivers of health-related judgments [61]; their design and analysis follow current methodological guidance for vignette data [62]. Each participant reads and evaluates all four scenarios of AI implementation (A–D), presented in a counterbalanced sequence. The within-subjects structure makes each respondent their own control, eliminating inter-individual variability from between-scenario comparisons and substantially increasing statistical power relative to a between-subjects design of the same size [63]. The presentation sequence is counterbalanced. The survey platform allocates participants at random, in equal proportions and independently of any participant characteristic, to one of the four sequences of a Williams (balanced Latin-square) design: A → B → C → D, B → D → A → C, C → A → D → B, and D → C → B → A. In this square, every scenario occupies every serial position exactly once, and every ordered pair of scenarios occurs exactly once, so that autonomy level is orthogonal both to serial position and to first-order carry-over, and an additive model containing a four-level autonomy effect and a four-level serial-position effect is fully identified. The theoretically motivated ascending sequence and its exact mirror image are retained as two of the four arms. A fixed ascending presentation would have mirrored the progressive continuum under investigation and given every participant an identical evaluation context, but it would have left order, carry-over, and fatigue effects inseparable from the autonomy gradient; because H1–H3 concern precisely that gradient, internal validity was given priority over uniformity of context. Counterbalancing also makes the embedded manipulation check diagnostic rather than merely descriptive: perceived AI control should track the described autonomy level within every sequence, whereas an anchoring or fatigue artifact would instead track serial position—a distinction that a monotonic manipulation-check profile obtained under a fixed order cannot draw. Presentation sequence is therefore retained as a between-subjects factor in all primary models, a second manipulation check (perceived technical sophistication) separates autonomy from technical complexity, and a per-scenario difficulty item indexes fatigue (Section 2.6, Section 2.7, Section 2.8, and Section 2.9.1). The study involves no medical, pharmacological, or surgical intervention. Reporting of the completed study will follow current recommendations for effect-size-based reporting [64] and, for the web-survey component, the CHERRIES checklist as operationalized in recent methodological guidance [65]. Publication of the protocol in advance of data collection is intended to reduce publication bias and analytic flexibility [66,67].

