
### 2.2. Experimental Vignettes

The four vignettes describe distinct configurations of AI involvement in facial reconstructive surgical planning, varying both the AI’s task (imaging analysis, decision support, outcome simulation, autonomous planning) and the surgeon’s level of supervision (Table 1). Each configuration corresponds to a capability documented in the current literature: anatomical structure analysis from CT [6,8], algorithmic generation of candidate surgical plans [9], three-dimensional simulation of postoperative facial appearance [12,13], and highly autonomous planning of the kind anticipated by surgical-autonomy frameworks [14,15]. All vignettes open with an identical premise (the respondent needs facial reconstructive surgery following an injury) and are written in parallel second-person wording of comparable length and reading difficulty, so that scenario content—not framing—drives differences in responses. Because the four configurations differ in what the AI does as well as in how much the surgeon decides, a perceived difference between them could in principle reflect technical sophistication rather than autonomy. Three features are intended to keep the two apart. First, every vignette closes by stating explicitly how the final surgical plan is reached and by whom. In Scenarios A–C, a single clause of parallel construction names the surgeon as the decision-maker (making all decisions, choosing among the proposed options, or deciding the final plan after reviewing the simulations); in Scenario D, the closing sentences state that the surgeon reviews the AI’s plan but rarely modifies it. What varies is therefore the decisional locus, not the computational task. Each comprehension check is built on that same feature: the decision-maker in Scenarios A and B; the role of the system in Scenario C (whose decisional clause is functionally equivalent to Scenario B’s, so that the role is what distinguishes the two); and the origin of the plan actually followed in Scenario D. Second, the vignettes are matched on the quantity of technical detail supplied—one sentence describing the system’s input and output in each case—so that described sophistication does not rise in step with autonomy. Scenario C specifies a generative three-dimensional simulation, computationally the most elaborate output in the set, yet leaves the decision entirely with the surgeon; Scenario D describes a comparatively conventional optimization whose distinguishing feature is decisional rather than technical. Third, two manipulation checks follow every scenario: MAN1, perceived control of the AI over the final decision, and MAN2, perceived technical sophistication of the system. The manipulation is treated as valid only if MAN1 orders the scenarios as intended; MAN2 verifies that sophistication does not itself increase monotonically with autonomy and enters a pre-specified sensitivity analysis as a covariate, so that the autonomy effect can be estimated with perceived sophistication held constant (Section 2.9.1). The full vignette texts are provided in Appendix A.

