
### 2.8. Pilot Study and Instrument Validation

The instrument will be validated in a pilot study (*N* = 50, not included in the main sample, allocated 1:1 to the ascending sequence A → B → C → D and to its exact reverse D → C → B → A) before the main study is launched. The pilot will estimate (i) internal consistency—Cronbach’s α and McDonald’s ω with 95% confidence intervals for each three-item composite, computed separately per scenario, against a threshold of ≥0.70, with ω reported alongside α in line with current psychometric guidance [73]; with three items per construct, α ≥ 0.70 requires a mean inter-item correlation of only $\bar{r}$ ≥ 0.44 under the generalized Spearman–Brown relation (Figure 2), a realistic requirement for parallel items; (ii) inter-item correlations (flagged at r > 0.90 for redundancy or r < 0.20 for heterogeneity) and corrected item-total correlations (threshold ≥ 0.40), plus the correlation between repeated measurements, reported with a 95% confidence interval, to verify the ρ ≈ 0.50 planning assumption and, where it is not met, to trigger the adaptive sample-size rule of Section 2.5; (iii) the factor structure of the nine response items, via exploratory factor analysis (principal-axis extraction, oblique rotation, sampling adequacy KMO ≥ 0.70, Bartlett’s test of sphericity, parallel analysis as the retention criterion)—an anticipated risk is that acceptability and trust items form a single factor, in which case the two constructs will be merged into a single “trust–acceptance” score and the analysis plan adjusted transparently before pre-registration, with this decision taken exclusively on pilot data; (iv) first-attempt comprehension-check pass rates per scenario (threshold ≥ 70%); (v) manipulation validity—MAN1 scores must order the scenarios from A to D in both pilot arms, while MAN2 (perceived technical sophistication) must not increase monotonically with autonomy; if it does, the vignettes will be reworded to equalize the described sophistication of the systems and the check repeated before pre-registration; (vi) fatigue—perceived difficulty (DIF1) and section-wise drop-out across serial positions in both arms; (vii) cognitive interviews with 5–8 participants to identify confusing wording, probing in particular whether RES1–RES6 are read in the intended senses of moral answerability, outcome-independent accountability, and legal fault (Section 2.6); and (viii) a first bound on order effects—the two pilot arms are compared on the three composites and on MAN1 by a scenario × order mixed ANOVA (*n* = 25 per arm; minimum detectable interaction *f* = 0.17 at ρ = 0.50), which can exclude medium-to-large order artifacts but not small ones, the definitive test being the main-study interaction. The four-sequence randomizer used in the main study is implemented in the same pilot build. Because the pilot itself exercises only two of the four arms, the randomizer is verified there by simulated allocation, which also confirms that the allocated sequence and the serial position of each scenario are stored correctly. A ninth objective is included: (ix) the keying and dimensionality of the four general-attitude items (G1–G4), since G3 is a caution item that the present scoring treats as positively keyed while G2 and G4 are reversed; the scoring rule for that block is fixed on pilot data before pre-registration, and if the four items do not form a single interpretable dimension they will enter the person-level analyses individually rather than as a composite. Because a sample of 50 is at the lower limit for stable factor solutions, the pilot EFA is treated as provisional: the factor structure will be re-examined by confirmatory factor analysis on the main sample (*N* = 300), with acceptable fit defined a priori as CFI/TLI ≥ 0.95, RMSEA ≤ 0.06, and SRMR ≤ 0.08. Because the same nine items are answered four times, longitudinal measurement invariance across the four scenario repetitions (configural, metric, and scalar) will also be tested on the main sample; at least partial scalar invariance is required for the between-scenario comparison of composite means, and any non-invariant item will be reported and handled by partial-invariance modeling. Pilot results will be reported in the methods section of the results article.

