
### 2.9. Statistical Analysis

#### 2.9.1. Primary Analyses

Each composite score (acceptability, trust, perceived risk) will be analyzed by a mixed repeated-measures ANOVA, with autonomy level (four scenarios) as the within-subjects factor and presentation sequence (four Williams sequences) as the between-subjects factor. The Greenhouse–Geisser correction will be applied when Mauchly’s test indicates a sphericity violation (Huynh–Feldt for ε between 0.75 and 1), and the multivariate approach (Pillai’s criterion) will be reported in parallel as a sphericity-robust check. H1 and H2 will be tested with within-subjects trend contrasts across the autonomy gradient. Because acceptance need not fall in a straight line, the complete set of orthogonal polynomial contrasts—linear, quadratic, and cubic—is pre-specified, and each is reported together with the proportion of the omnibus effect it accounts for. A purely linear profile leaves the quadratic and cubic components negligible, whereas a step between two adjacent levels appears as a large linear component accompanied by a substantial quadratic or cubic one. Because every monotone step is linear-dominant, the polynomial decomposition establishes departure from a straight line but cannot by itself locate the break; the break is identified only from the Holm-corrected adjacent-pair contrasts (A–B, B–C, C–D). A quadratic-dominant profile with a small linear component would instead indicate a non-monotone pattern, which the hypotheses do not predict and which would be reported as such. A non-monotonic or threshold pattern will be reported as such rather than summarized by the linear trend alone. Post hoc comparisons use dependent-samples *t*-tests for the six scenario pairs with Holm’s sequential correction, applied within each hypothesis-defined family of tests in line with current guidance on multiplicity control [74]. Effect sizes will be reported as partial η^2^ for omnibus tests and Cohen’s dz for pairwise comparisons, with 95% confidence intervals, following effect-size-centered reporting recommendations [64]. Assumption checks include graphical inspection of difference-score distributions; as a distributional robustness analysis, the Friedman test with Holm-corrected Wilcoxon signed-rank pairwise comparisons will be reported alongside each primary test—supplemented by ordinal (cumulative-link) models as sensitivity analyses for the Likert-based outcomes [71]—and the concordance of parametric and nonparametric conclusions stated explicitly. Order dependence is tested directly as the scenario × sequence interaction; a non-significant interaction, together with equivalence of the four sequence-specific profiles, supports pooling across sequences. Independently of that test, the autonomy effect is re-estimated from a linear mixed model with random intercepts per participant and additive fixed effects of autonomy level and serial position (1–4). The Williams square renders this model identified, so the estimate is adjusted for arbitrary—not merely linear—serial-position and fatigue effects, while first-order carry-over is balanced by the design rather than modeled; position-adjusted and unadjusted estimates are reported side by side, and any material divergence between them is treated as evidence of an order artifact and interpreted accordingly. Perceived difficulty (DIF1) and perceived technical sophistication (MAN2) are each added as time-varying covariates in further sensitivity models, addressing fatigue and the possibility that responses track the apparent complexity of the system rather than its autonomy. Finally, between-person heterogeneity in response profiles is examined by adding a random slope for the linear autonomy contrast and testing the improvement in fit by a likelihood-ratio test; a substantial random-slope variance indicates that an average trajectory conceals distinct response patterns and licenses the exploratory typology described in Section 2.9.2. Because a non-significant test is not evidence of absence, a smallest effect size of interest of *dz* = 0.20—the value detectable at the Bonferroni bound for the six pairwise contrasts at *N* = 300—is fixed in advance, and equivalence testing by two one-sided tests against that bound is reported alongside every null pairwise result, so that any claim that two adjacent scenarios do not differ rests on an equivalence test rather than on the absence of significance.

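### The MAN2 rule (no monotone increase with autonomy) can pass while perceived sophistication rises steeply from A to C, so a pass separates autonomy from sophistication only at C–D

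*Protocol article*

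**What the plan says.** Section 2.2 concedes that the vignettes differ in what the AI does as well as in who decides, and lists three safeguards: a closing clause on how the plan is reached, one matched sentence of technical detail per vignette, and the two manipulation checks. The matching is done "so that described sophistication does not rise in step with autonomy". Section 2.1 gives the second check a strong role: "a second manipulation check (perceived technical sophistication) separates autonomy from technical complexity".

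The criterion itself is narrower. Section 2.2: "MAN2 verifies that sophistication does not itself increase monotonically with autonomy and enters a pre-specified sensitivity analysis as a covariate". Section 2.8, for the pilot: "MAN2 (perceived technical sophistication) must not increase monotonically with autonomy". The consequence follows there: "if it does, the vignettes will be reworded to equalize the described sophistication of the systems and the check repeated before pre-registration". No bound is set on the A–D difference, the slope or any pairwise increase in MAN2.

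On the vignettes, Section 2.2 states: "Scenario C specifies a generative three-dimensional simulation, computationally the most elaborate output in the set, yet leaves the decision entirely with the surgeon". D is described there as technically more conventional than C.

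On the analysis, Section 2.9.1 states: "H1 and H2 will be tested with within-subjects trend contrasts across the autonomy gradient". It locates any break from the adjacent pairs A–B, B–C and C–D. Table 5 adds a mixed ANOVA on MAN2 and re-estimation of the primary models with MAN2 as a time-varying covariate, and Section 2.9.2(ix) adds manipulation-check profiles by sequence.

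**The concern.** Absence of a monotone rise is much weaker than absence of association. With four ordered levels, a single reversal passes the rule however large the other two steps are, and the vignettes are written so that a reversal at C–D is the intended perception. The check then says nothing about A to B to C, or about D relative to A.

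What is at stake is the reading of the gradient. If MAN2 rises from A to C and dips slightly at D, then A–B, B–C, A–C, A–D and the linear trend each combine a change in autonomy with a change in perceived sophistication, while the study would hold a passed check said to separate the two. B–C is the most exposed pair, because Section 2.2 itself treats the closing decision clauses of B and C as functionally equivalent while making C technically more elaborate.

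**Working it through.** **Inputs from the protocol.** Pilot N = 50; planning ρ = 0.50, with 0.30 as the conservative value (Section 2.5); four scenarios.

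**Assumptions.** The article gives no SD for MAN2 and does not say whether observed means or a test decide. I take pooled observed means, an item SD of 1 to 2 on the 1–7 scale, and ρ of 0.3 to 0.5 (in the article, a planning range for composites). The mean profiles are illustrations, not predictions.

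**The plan's own figure.** The MAN2 rule carries no number. The nearest is the pilot order bound, f = 0.17 at N = 50 and ρ = 0.50. With λ = N·m·f²/(1 − ρ) and m = 4, f = 0.167 gives λ = 200 × 0.0279/0.5 ≈ 11.2 on 3 and 144 df, which is power 0.80. The figure reproduces.

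**How closely a passing profile can follow autonomy.** Correlate the four means with ranks 1–4 (sum of squares of the ranks = 5).

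- 3.5/4.5/6.0/5.5: deviations from 4.875 are −1.375, −0.375, 1.125, 0.625. The cross-product with (−1.5, −0.5, 0.5, 1.5) is 3.75 and the sum of squares is 3.6875. r = 3.75/√(5 × 3.6875) = 0.87, so 76% of the between-scenario variation is linear.
- 3.0/4.0/5.0/4.8: the cross-product is 3.2 and the sum of squares 2.48. r = 3.2/√(5 × 2.48) = 0.91, so 83% is linear.

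Both profiles satisfy the rule, because D lies below C. D is nevertheless 2.0 and 1.8 points above A.

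**How often the pilot would pass them.** The SE of a difference between two scenario means is SD·√(2(1 − ρ)/N). It runs from 1 × √(2 × 0.5/50) = 0.141 to 2 × √(2 × 0.7/50) = 0.335. The A–B and B–C steps are 1.0 or more, about 3 SE or above, so a pass comes almost entirely from an observed C-to-D dip, with probability Φ((C − D)/SE).

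| True means | C − D | SE 0.141 | SE 0.335 |
|---|---|---|---|
| 3.5/4.5/6.0/5.5 | 0.5 | Φ(3.54) ≈ 1.00 | Φ(1.49) = 0.93 |
| 3.0/4.0/5.0/4.8 | 0.2 | Φ(1.41) = 0.92 | Φ(0.60) = 0.73 |

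Simulating all four means gives the same ranges, 93–100% and 73–92%.

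**Would a bound on the overall rise catch these?** At the largest SE, the lower 95% limit of the A–D difference is about 2.0 − 1.96 × 0.335 = 1.34 for the first profile and 1.8 − 0.66 = 1.14 for the second. Both are far from zero.

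**Would a limit on each adjacent step be better?** No. Take 4/4/5/4, where only C is more elaborate (r = 0.26, A–D difference 0). A 0.5-point limit on B–C would be exceeded with probability Φ((1.0 − 0.5)/SE), about 93–100%, and would reword away the contrast that C was written to provide.

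**The rule also misfires the other way.** Means of 4.00/4.01/4.02/4.03 fail it, although the four scenarios are practically equal.

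**The case against.** **The gate is not the whole argument.** A reader might infer that a MAN2 pass is the plan's sole ground for crediting autonomy. The article does not say so: Section 2.2 also relies on the decision clause and the matched detail, and makes validity of the manipulation conditional on MAN1. That stands, and it limits the consequence.

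**MAN2 is examined again at N = 300.** The MAN2 ANOVA, the profiles by sequence and the MAN2-adjusted means would make a steep rise visible. This also stands. But no interpretation changes on any of them, whereas for serial position Section 2.9.1 does say what a material divergence would mean.

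**C is a deliberate dissociation.** If C is rated at or above D, a fall in acceptability from C to D cannot come from higher perceived sophistication, and Section 3 expects the largest drop there. A reader might infer that the whole gradient is confounded; C–D is not, on that condition.

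**The numbers are assumed.** The SD and the mean profiles are not in the article, and a reader might infer that MAN2 will in fact follow autonomy. Nothing in the article shows that. The illustration shows only that the rule could not tell. Whether monotone means strictly increasing or non-decreasing matters only for exact ties.

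**The covariate model.** MAN2 is rated after acceptability, trust and risk in the same block (Section 2.6), so its slope may carry over from those ratings. A reader might infer a definite bias in the adjusted estimate; without a known slope its size cannot be given. What follows is that the adjustment supports an association, not an effect at fixed sophistication.

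**Conclusion.** Wrong as written. Followed exactly, the rule passes profiles in which most between-scenario variation in MAN2 is linear in autonomy: 76% and 83% in the two examples, passing in about 93–100% and 73–92% of pilots under the assumptions above. The statement that the check separates autonomy from complexity is therefore unsupported by a pass for A–B, B–C, A–C, A–D and the linear trend. It remains supported for C–D when MAN2 of D does not exceed that of C. The logical point needs no assumed value; only the pass rates do. The other safeguards and the main-study MAN2 analyses reduce the harm but do not repair the gate.

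**What to change.** 1. **Pilot.** Replace the monotonicity rule with a bound on the overall MAN2 rise (A–D difference or linear slope), with a margin fixed in advance, a 95% confidence interval, and a statement of which limit decides. Reword only if that bound is breached. Do not add an adjacent-step trigger, because C is deliberately more elaborate. The margin must respect pilot precision: the half-width for A–D is about 1.96 × 0.141 = 0.28 to 1.96 × 0.335 = 0.66 points under the same assumptions.
2. **Main study.** Attribute a difference to autonomy rather than sophistication only for pairs whose MAN2 increase has an upper 95% limit below the margin. Report other pairs as joint autonomy-plus-sophistication differences, and the linear trend likewise where the overall bound is breached. Name C–D as the key separating contrast, provided MAN2 of D does not exceed that of C. At N = 300 and SD 1.5, ρ = 0.5, the SE of a MAN2 difference is 1.5 × √(2 × 0.5/300) = 0.09, so this is workable.
3. **Wording.** Describe the MAN2-adjusted model as an association-based sensitivity analysis, since MAN2 is a post-exposure rating taken after the outcomes.

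Cost: one pilot criterion, one reporting rule and one sentence, all before pre-registration, with no new items and no change to the planned sample sizes. The downside is that the pilot may call for rewording and a repeat check more often, and some pairs may lose the autonomy-only label.
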